### Resources

The program requires the following resources:Physical space for sessions and assessments.Simple musical instruments: maracas, drums, xylophones, and tambourines.Audio equipment: speakers, music players, and microphones.Relaxation support materials: cushions and ergonomic chairs.

### Special considerations

Individual adaptation: Activities will be tailored to the functional, cognitive, and emotional levels of each participant.Psychological follow-up: In cases where relevant emotional symptoms are detected, psychological support will be recommended.Family involvement: Family participation will be encouraged to provide continuous support and to foster a therapeutic environment at home.

### Data management

All data will be stored in a secure database accessible only to the authorized research team. Confidentiality will be ensured in accordance with current data protection regulations, and all personal information will be anonymized prior to analysis.

### Oversight and monitoring

The study will be coordinated by the principal research team, which will oversee recruitment, intervention, and data collection. Given the low-risk nature of this non-invasive, non-pharmacological intervention, an independent data monitoring committee will not be established.

### Dissemination policy

The results of the study will be disseminated through publications in scientific journals and presentations at specialized conferences. Participants requesting feedback will be provided with a summary of the study findings.

### Statistical analysis

Statistical analysis will be carried out using Jamovi (version 2.7.26). Qualitative variables will be described using frequencies (N) and percentages (%). Number of observations (N), mean, median, standard deviation, minimum, and maximum will be used to describe quantitative variables. Missing data will be reported descriptively, including the extent and pattern of missingness across time points.

Baseline demographic and clinical characteristics will be described. The outcome measures will be calculated according to their guidelines. Scores will be reported at all time points (baseline, 5 weeks, 10 weeks, and 3-month follow-up). A linear mixed-effects model (MLM) will be carried out to estimate the main effect of the intervention on the primary outcome, motor function assessed using the FMA. Additional models will be conducted to estimate the secondary motor outcome, upper-limb motor function assessed using the ARAT. Exploratory models will be conducted for cognitive flexibility (WCST), self-perceived executive functioning (BRIEF-A), and stroke-specific quality of life (SS-QOL). These exploratory analyses will be interpreted cautiously and will be used to inform future research rather than to establish definitive efficacy in these domains. The model will include time, group, and the interaction between group and time as fixed effects. Time after stroke will be included as a covariate to account for variability related to recovery stage. A random intercept will be specified to account for repeated measures. Model parameters will be estimated using restricted maximum likelihood (REML), which allows analysis without assuming sphericity. Degrees of freedom will be computed using the Satterthwaite method.

To explore agreement between participant and family member reports on the BRIEF-A executive function questionnaire, additional analyses will be carried out using intraclass correlation coefficients (ICC). Bland–Altman plots will be used to assess systematic bias and limits of agreement between informants.

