### Study design

This is a prospective, phased, randomized waitlist-controlled intervention study with a parallel-group design, aimed primarily at evaluating the effects of the intervention on motor function. Upper-limb motor function will be assessed as a secondary motor outcome, while executive functioning and stroke-specific quality of life will be examined as exploratory outcomes. Participants will be randomly allocated to either an experimental group or a control/waitlist group.

The study will be implemented in successive recruitment phases. The first phase will be conducted in a single outpatient neurological rehabilitation center in the Community of Madrid, Spain, and subsequent phases will extend recruitment to additional outpatient neurological rehabilitation centers within the Community of Madrid until the required total sample size is achieved.

In the first recruitment phase, approximately 24 participants are expected to be included, with 12 participants allocated to each group. Recruitment will then continue in subsequent phases across additional centers, maintaining the same eligibility criteria, intervention protocol, assessment schedule, randomization procedures, and outcome measures, until the planned sample of 76 participants is reached.

Two groups will undergo the same overall rehabilitation process. Over a total of 5 weeks (two sessions per week), the experimental group will receive their standard rehabilitation care complemented by a program of music-based activities. The control/waitlist group will receive only standard rehabilitation care during the first 5-week intervention period and will subsequently undergo the music-based program after the experimental group has completed it, thereby effectively switching their roles.

This design ensures that all participants benefit from the intervention while allowing temporal comparison between the groups. This structure is consistent with previous studies of similar music-based rehabilitation programs and supports ethical rigor by ensuring that all participants receive a potentially beneficial intervention.

All participants will be assessed at baseline (week 0), after 5 weeks (post-intervention), and again at 10 weeks (after crossover). A 3-month follow-up will be conducted to explore the maintenance of potential effects.

The study has been preregistered in OSF Registries.^1^ This record is reported as an open science preregistration and is not presented as a clinical trial registry.

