### Sample size

The sample size was calculated following recommendations for comparing two means in intervention studies (23). As the Fugl-Meyer Assessment (FMA) was the main outcome, change in this measure was selected as the primary criterion. Following previous research (24), the minimal difference in scores used to detect between-group differences in motor improvement was 4, assuming a standard deviation of 12. Using a two-tailed t-test for the difference between means with 80% power and a 5% level of significance, the sample size required was 70 participants, with 35 per group. Considering a dropout rate of 10%, the final required sample size was estimated at 76 participants, with 38 per group.

Given the specificity of the target population and the outpatient rehabilitation context, recruitment will be conducted in successive phases. The first recruitment phase, conducted in a single center, is expected to include approximately 24 eligible and recruitable participants, with 12 participants per group. Subsequent phases will include additional outpatient neurological rehabilitation centers in the Community of Madrid until the total required sample size of 76 participants is reached. Based on the projected recruitment capacity across participating centers, completion of recruitment is expected within approximately 1 year.

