### Follow-up

A follow-up interview will be scheduled 3 months after completion of the intervention to explore the maintenance of potential effects, the continued use of music-based strategies at home, and participants’ perceived acceptability, usefulness, and relevance of the intervention in their daily lives.

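### The primary model targets a main effect across four visits, but only week 5 compares treated with untreated participants, and that contrast is never named as primary

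*Protocol article*

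**What the plan says.** The Statistical analysis section sets the target of the primary analysis: "A linear mixed-effects model (MLM) will be carried out to estimate the main effect of the intervention on the primary outcome". The outcome is the FMA motor score. The same section specifies the terms: "The model will include time, group, and the interaction between group and time as fixed effects". It adds time since stroke as a covariate and a random intercept. The Abstract gives the same target and the same fixed effects. Scores are reported at baseline, 5 weeks, 10 weeks and 3 months, and the section on dropout and missing data says that the models use all available repeated measures.

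Under Study design, the waitlist group "will subsequently undergo the music-based program after the experimental group has completed it". The Assessment section describes week 5 as the comparison of the experimental group with the waitlist group, and week 10 as an evaluation of both groups once the intervention is complete.

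The Sample size section rests on one comparison of two groups: "Using a two-tailed t-test for the difference between means with 80% power and a 5% level of significance", where "the minimal difference in scores used to detect between-group differences in motor improvement was 4, assuming a standard deviation of 12".

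The Follow-up section states: "A follow-up interview will be scheduled 3 months after completion of the intervention". It does not say whose completion is meant. Table 2 shows a single 3-month column after week 10.

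**The concern.** In a model that contains group, time and their interaction, *main effect* has a technical meaning: the group difference averaged over visits. In this design that average combines one informative visit with a baseline visit at which nobody has been treated and two visits by which both groups have been treated. If the intervention works and the waitlist group catches up, the averaged term moves towards zero because the waitlist group benefited.

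The obvious alternative, the overall group-by-time test, has the opposite weakness. It gives no direction or size, and it responds to a difference at any visit, including visits without an untreated comparator.

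The primary question is therefore not tied to one number. Several terms from the same fitted model could later be presented as the primary result, and the one literally named is the one least likely to show a real effect.

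**Working it through.** **Inputs from the protocol.** Difference 4, SD 12, 35 per group, two-sided 5%, 80% power (Sample size). Four visits (Assessment; Statistical analysis). A random intercept, which implies one common correlation ρ between visits (Statistical analysis).

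**Assumptions not in the protocol.** SD 12 is the SD of scores; ρ lies between 0.5 and 0.9; the expected baseline difference is 0; there are no missing data; the normal approximation applies; the post-crossover patterns are those in step 3.

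**Step 1: the plan's own figure.** For two means, n per group = 2 × (1.960 + 0.842)² × 12² / 4² = 141.3, so 142 (143 with the exact t-test). The protocol states that "the sample size required was 70 participants, with 35 per group". The figure does not reproduce: with SD 12 applied directly to the compared quantity, 35 per group gives about 28% to 29% power. This is a separate point. It matters here only because 80% power cannot be assumed for any contrast.

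**Step 2: exposure by visit.**

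| Visit | Experimental group | Waitlist group | Treated v untreated? |
|---|---|---|---|
| Week 0 | untreated | untreated | no |
| Week 5 | treated | untreated | yes |
| Week 10 | treated | treated | no |
| 3 months | treated | treated | no |

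**Step 3: the averaged group effect.** With dₜ the experimental-minus-waitlist difference at visit t, the averaged effect is (d₀ + d₅ + d₁₀ + d_FU) / 4. Set d₀ = 0 and d₅ = 4.

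| Assumed pattern after crossover | d₁₀, d_FU | Averaged effect | Week 5 minus baseline |
|---|---|---|---|
| Full catch-up | 0, 0 | 1.0 | 4.0 |
| Half at week 10, then full | 2, 0 | 1.5 | 4.0 |
| Half at both | 2, 2 | 2.0 | 4.0 |
| None | 4, 4 | 3.0 | 4.0 |
| Experimental group 2 behind at week 10, then equal | −2, 0 | 0.5 | 4.0 |

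The dilution runs from 4/3.0 = 1.3-fold to 4/0.5 = 8-fold. The week-5 contrast is 4.0 throughout.

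**Step 4: coding.** The averaged effect is what averaging (sum-to-zero) coding returns. If group is coded with baseline as the reference visit, the group coefficient is d₀. Its expected value under randomisation is 0, so it is not an effect estimate.

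**Step 5: precision at 35 per group.**
- Averaged effect: SE = 12 × √(2/35) × √((1 + 3ρ)/4), which is 2.27 at ρ = 0.5 and 2.76 at ρ = 0.9. With an effect of 1.0, power is about 6% to 7%. Even with no catch-up (3.0) it is about 19% to 26%.
- Week-5 change contrast: SE = 12 × √(2/35) × √(2(1 − ρ)), which is 2.87 at ρ = 0.5, 1.81 at 0.8 and 1.28 at 0.9. With an effect of 4.0, power is about 29%, 60% and 88%.

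**Step 6: the 3-df interaction.** The noncentrality is Σ(dₜ − d̄)² / [2 × 12² × (1 − ρ)/35]. For differences (0, 4, 0, 0), d̄ = 1 and the sum of squares is 1 + 9 + 1 + 1 = 12. At ρ = 0.8 the divisor is 57.6/35 = 1.646, the noncentrality is 7.3 and power is about 60%. For (0, 0, 4, 0) or (0, 0, 0, 4), with no week-5 effect at all, the sum of squares is again 12 and the rejection rate is the same.

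**Step 7: follow-up timing.** If the 3-month visit is anchored to each group's own completion (week 5 and week 10), time since randomisation differs by 10 − 5 = 5 weeks. If it falls on a common date, time since own treatment differs by 5 weeks. It is not like-for-like in either case.

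**The case against.** The best defence is that *main* means principal. The protocol refers to the effect of the intervention, not of group, and sets it against additional secondary and exploratory models. The interaction is in the model and yields the undiluted week-5 contrast. The Assessment section gives week 5 the comparative role, and the sample size concerns motor improvement. An analysis plan that is not shown could name the contrast.

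Much of this stands. Week-5 change is probably what the authors intend, and four stronger readings should be resisted:
- A reader might infer that the primary estimate will be diluted four-fold. That needs averaging coding and full catch-up at both later visits, and the protocol states neither.
- A reader might infer that naming the week-5 contrast secures about 80% power. With 35 per group and a 4-point difference, that needs a change SD of about 5.9, which appears nowhere in the protocol.
- A reader might call the later visits non-randomised. They still compare the groups as randomised; what they lack is an untreated comparator.
- A reader might take the 3-month visit as anchored separately in each group. The Follow-up section does not settle this.

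The defence does not remove the point. The protocol does more than leave a detail open: it states a target that, in its technical sense, does not fit the crossover. On the looser reading, the model still offers a group term, a 3-df interaction and several visit contrasts, and nothing says which one answers the primary question.

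**Conclusion.** The point holds as a mismatch between the stated target of the primary model and the design, which leaves the primary estimand ambiguous. That only week 5 contrasts treated with untreated participants follows from the protocol itself and needs no assumption. The size of the dilution does need assumptions: a 4-point week-5 difference would appear as 1.0 point under averaging coding with full catch-up, with a range of about 0.5 to 3.0 over the patterns tried. The power figures rest on the assumed correlation and on reading SD 12 as the SD of scores. Because this concerns the primary confirmatory test, it should be settled before recruitment begins.

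**What to change.** State one primary estimand: the between-group difference in FMA motor score at week 5, adjusted for baseline. Test it as one 1-df contrast, either the group-by-time term for week 5 versus baseline or the baseline-adjusted week-5 difference, and say which. Replace the main-effect wording in the Abstract and in Statistical analysis. Name the same contrast for ARAT and for the exploratory outcomes.

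Report week 10 and 3 months as secondary or descriptive comparisons of early versus delayed intervention, noting that they have no untreated comparator. State whether the 3-month visit is anchored to each group's own completion or to a common date.

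The cost is wording only. No new data or visits are needed, and the Study status section gives protocol version 1.0 with recruitment not yet started. The sample-size calculation needs its own correction; any power quoted for the week-5 contrast should state the within-person correlation assumed.

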#### Inclusion criteria

The inclusion criteria will include the following:Participants must be between 18 and 70 years of age. The upper age limit was established to reduce heterogeneity associated with age-related comorbidities and cognitive decline, which may influence rehabilitation outcomes and engagement in structured interventions. This range is also consistent with previous research on post-stroke rehabilitation and functional recovery mechanisms (6, 7).Participants must have a stroke diagnosis made at least 3 months prior to participation, corresponding to the late subacute phase (3–6 months post-stroke) and/or the chronic phase (>6 months), in line with commonly used temporal classifications of post-stroke recovery phases (5). These classifications distinguish subacute and chronic stages based on time since stroke onset, thereby helping to ensure clinical stability and reduce variability associated with earlier stages of recovery.Participants must have sufficient cognitive and receptive language abilities to understand and follow simple instructions, regardless of verbal expression capacity. Cognitive screening will be conducted using the Montreal Cognitive Assessment (MoCA), with a score of ≥18 used as the eligibility threshold. Receptive language and task comprehension will also be confirmed during screening through the ability to follow simple one-step verbal instructions.Participants must have a minimum functional ability to perform basic activities of daily living, defined as a Barthel Index score of ≥40, together with sufficient sitting tolerance and the ability to engage in structured activities, with support if needed. Participants must have sufficient motor ability to perform the planned intervention tasks, as determined during screening through observation of seated postural control and basic upper-limb performance on intervention-related tasks.Participants must not have severe pre-stroke cognitive or functional impairments, based on medical records and clinical history.

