### Outcomes

#### Primary outcome

##### Fugl-Meyer Assessment (FMA)

The FMA is a stroke-specific, performance-based measure designed to assess motor impairment following stroke. It evaluates motor functioning, balance, sensation, and joint functioning, with particular emphasis on voluntary movement patterns. In this study, the motor domain score (including the upper and lower extremity motor subscales) will be used as the primary outcome variable. The motor domain is composed of ordinal items assessing movement, coordination, and reflex activity. The FMA has demonstrated excellent reliability, validity, and responsiveness in stroke populations and is widely considered one of the gold-standard measures for assessing post-stroke motor function in clinical and research settings (31, 32). It was selected as the primary outcome due to its sensitivity to changes in motor performance and its extensive use in stroke rehabilitation trials, allowing comparison with previous studies. It will constitute the main variable for the primary inferential analysis, while the ARAT will be analyzed as a secondary motor outcome, and executive functioning and quality-of-life measures will be interpreted as exploratory outcomes. Items are scored on a 3-point ordinal scale (0–2) and summed to yield a total motor score ranging from 0 to 100, with higher scores indicating better motor function (31, 32).

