### Dropout and missing data management

Given the longitudinal design of the study, particular attention will be paid to participant retention and data completeness. Protocol completion will be defined as participation in at least 80% of the scheduled sessions (i.e., at least 8 of 10 sessions).

The primary analysis will follow the intention-to-treat (ITT) principle, including all randomized participants with available outcome data in the analysis set. Linear mixed-effects models will use all available repeated-measures data under the missing-at-random assumption, without formal imputation. The extent and patterns of missing data will be reported descriptively.

An additional per-protocol analysis will be conducted, including only participants who meet the predefined completion threshold.

Dropout rates, reasons for withdrawal, and patterns of missing data will be reported descriptively to support transparent interpretation of the study findings.

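### As specified, time after stroke adds almost no adjustment or precision to the week-5 group-by-time contrast, and the available gain from adjusting for baseline FMA is not taken

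*Protocol article*

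**What the plan says.** The Statistical analysis section of the protocol article fixes the primary model in some detail. It announces that "A linear mixed-effects model (MLM) will be carried out to estimate the main effect of the intervention on the primary outcome". On the terms it says: "The model will include time, group, and the interaction between group and time as fixed effects". It then adds: "Time after stroke will be included as a covariate to account for variability related to recovery stage", and "A random intercept will be specified to account for repeated measures". The abstract repeats the fixed effects and the covariate. Neither place gives time after stroke an interaction with time or group, and neither names baseline FMA as a covariate.

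The Assessment section and Table 2 schedule the FMA at week 0, week 5, week 10 and the 3-month follow-up. The Dropout and missing data management section says: "Linear mixed-effects models will use all available repeated-measures data under the missing-at-random assumption, without formal imputation". On the plain reading, baseline is therefore one of four repeated responses.

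The population is mixed in recovery stage. The entry rule is: "Participants must have a stroke diagnosis made at least 3 months prior to participation", and the same criterion covers both the 3 to 6 month and the later chronic stage. Allocation is by simple randomisation, with no stratification by stage. The Sample size section takes change in FMA as its criterion.

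**The concern.** The intervention effect has to be read from the week-5 comparison. By week 10 the waitlist arm has also had the programme, so later visits no longer compare treated with untreated participants. In the stated model, that effect is the group-by-time term for week 5 against baseline, which is a difference in within-person change.

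Time after stroke, taken at entry, is constant within a person. As a main effect it moves a participant's whole profile up or down and drops out of every change. It cannot represent early-stage participants improving faster over five weeks than chronic ones, which is the way recovery stage could bear on this contrast. A report could then describe the effect as adjusted for time after stroke when the adjustment had left it almost untouched.

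Separately, a baseline value that enters only as a response gives a change-score comparison. Precision that baseline adjustment would supply from data already collected is given up.

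**Working it through.** The plan gives no figure of its own for this contrast, so there is none to reproduce. The Sample size section supplies a difference of 4, an SD of 12 and 38 per group. The within-person correlation ρ, the strength of time after stroke as a predictor and the dropout mechanism are not in the document and are assumed below.

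**Step 1, algebra.** For participant i at visit j, with group g and time after stroke x, the stated model is

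Y_ij = α + τ_j + γ·g_i + δ_j·g_i + β·x_i + b_i + e_ij.

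Subtracting baseline (j = 0) from week 5 (j = 1):

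Y_i1 − Y_i0 = (τ_1 − τ_0) + δ_1·g_i + (e_i1 − e_i0).

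The terms γ·g_i, β·x_i and b_i all cancel. With complete data the estimate of δ_1 is the difference in mean change, whether or not x is in the model. Had x been given a visit-specific slope β_j, the term (β_1 − β_0)·x_i would remain.

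**Step 2, simulation.** Settings: 38 per arm, 4 visits, SD 12, week-5 effect 4, ρ = 0.8, time after stroke explaining 25% of the outcome variance but not predicting change, dropout depending on time after stroke, and 150 trials per scenario. Random-intercept REML fits without and with the covariate as a main effect gave, for the week-5 contrast:

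| Dropout | Mean shift in estimate | Largest shift | SE without | SE with |
|---|---|---|---|---|
| None | 0 | 9e-14 | 1.737 | 1.737 |
| About 10% | 0.06 | 0.27 | 1.773 | 1.771 |
| About 20% | 0.07 | 0.34 | 1.802 | 1.799 |

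In the same complete-data runs the covariate did affect other parts of the model. The random-intercept variance fell from 113 to 78 (31%), and the SE of the group coefficient fell from 2.72 to 2.37 (13%). Adding covariate-by-visit terms gave an SE of 1.749 for the week-5 contrast, 0.7% above 1.737. That is the price when recovery stage does not predict change.

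**Step 3, baseline adjustment.** With n per arm and score SD σ:

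- Change score: SE = sqrt(2 × 2(1 − ρ) × σ² / n). At ρ = 0.8: sqrt(2 × 0.4 × 144 / 38) = 1.741.
- Baseline as covariate: SE = sqrt(2 × (1 − ρ²) × σ² / n). At ρ = 0.8: sqrt(2 × 0.36 × 144 / 38) = 1.652.
- Ratio of SEs: sqrt((1 + ρ) / 2).

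| ρ (assumed) | Ratio of SEs | Reduction |
|---|---|---|
| 0.5 | 0.866 | 13% |
| 0.7 | 0.922 | 8% |
| 0.8 | 0.949 | 5% |
| 0.9 | 0.975 | 3% |

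The simulated model-based SEs at ρ = 0.8 agree (1.737 and 1.650). The spread of the estimates over only 150 trials did not show the gain (SD 1.77 with baseline as covariate, 1.72 without). Repeating the complete-data setting with 20,000 trials gave 1.65 against 1.73, in line with the formula.

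**The case against.** Several stronger readings are tempting, and the document does not support them.

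- A reader might infer that the covariate does nothing at all. It absorbs between-person variability, and the text promises only to account for variability, not to adjust recovery rates. Exact cancellation also needs complete data. The plan allows for 10% dropout and assumes data missing at random, where the covariate may condition on a predictor of dropout. This stands, but the movement in the week-5 contrast is small. The group coefficient that the covariate sharpens cannot be the treatment effect: it is either the pre-treatment difference or an average that includes visits after the waitlist arm has been treated.
- A reader might infer that the estimate is confounded by spontaneous recovery. Allocation is randomised and concealed, so imbalance in recovery stage is chance error that the SE already reflects. The issue is efficiency and accurate description, not bias.
- A reader might infer that baseline FMA is ignored. It is used as a response, which makes the contrast a change from baseline and matches the sample-size criterion. It is unused only as a covariate.
- A reader might infer a large gain in power. With 35 per group, a difference of 4 and SD 12 read as the SD of scores, a normal approximation gives 29% rising to 36% at ρ = 0.5, but only 88% rising to 89% at ρ = 0.9. With no ρ in the document, the most favourable value should not stand alone.

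It can also be said that contrasts and interaction terms are often left to an analysis plan, which is not shown here. That is fair for the naming of the contrast. It is weaker for the model, because the article already fixes the fixed effects, covariate, random term, estimator and degrees of freedom.

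**Conclusion.** The point holds as one of efficiency and specification. As written, time after stroke gives essentially no adjustment or precision to the week-5 group-by-time contrast: none with complete data, and a shift of 0.06 to 0.07 points on average (at most 0.34) with about 10% to 20% dropout under the simulated assumptions. The planned contrast is a valid change-score comparison, but its SE is larger than it need be. Baseline adjustment would reduce it by 13% to 3% for ρ from 0.5 to 0.9.

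This rests on three readings: baseline is one of the modelled visits, time after stroke is the value at entry, and the covariate has no interaction with visit. The text states nothing to the contrary on any of them. The size of the gain depends on ρ, which the trial's own data would have to supply.

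**What to change.** Before recruitment starts, revise the model description as follows.

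- State that the primary contrast is the between-group difference in FMA at week 5, in place of a general reference to the effect of the intervention.
- Estimate it in the mixed model with baseline FMA adjusted for, in one of two ways: baseline as a covariate with the post-baseline visits as responses, or all four visits as responses with baseline means constrained equal across arms. The second keeps all available data, as the missing-data section intends. A week-5 analysis of covariance alone is not strictly equivalent, because it drops anyone without a week-5 score.
- Decide what time after stroke is for. If it is meant to adjust the week-5 contrast for recovery stage, enter it with a time-after-stroke by visit term. If it is meant only to absorb between-person variability, say so and do not describe the contrast as adjusted for recovery stage.
- Use the same form for the ARAT, WCST, BRIEF-A and SS-QOL models.

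The cost is a few model terms and degrees of freedom. The interaction may raise the SE slightly if recovery stage does not predict change (1.737 to 1.749 in the simulation). All variables are already collected.
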